### Part 2:Wearable device assessment (IDEEA)

2.11

In addition to laboratory-based measurements, a wearable micro-inertial sensor system (IDEEA, Intelligent Device for Energy Expenditure and Activity) will be used to quantify lower limb kinematics in a real-world setting. The IDEEA system used in this study is manufactured in China and provided by Hefei Minglisun Electronics Co., Ltd. (brand: MiniSun). The IDEEA assessment is conducted separately in a real-world stair climbing environment and is not synchronized with the laboratory-based measurements (20). The IDEEA system uses high-frequency multi-sensor fusion (accelerometer and gyroscope) to record spatiotemporal parameters including walking speed, step frequency, and double support time, as well as kinetic characteristics such as mean power and pulling acceleration (21).

#### Testing procedures

2.11.1

Participants will wear the IDEEA system while performing a continuous stair climbing test on a standard architectural staircase (step height: 14 cm, depth: 27 cm, slope: approximately 27.4°, 18 steps with a mid-stair landing) (22). Under no external verbal interference and without using handrails, participants will ascend the 18 steps at their natural walking pace without stopping, for three consecutive trials (22).

#### Data extraction

2.11.2

Gait parameters during stair climbing will be exported using the IDEEA system software, and the arithmetic mean of the three trials will be used for statistical analysis. The following parameters will be extracted: kinetic parameters including mean power (W) and pulling acceleration (g); and spatiotemporal gait parameters including walking speed (m/s), step frequency (steps/min), and double support time (ms).

#### Rationale for stair climbing as a test activity

2.11.3

Stair climbing is a high-load daily activity that requires the knee joint (particularly the patellofemoral joint) to generate and withstand significant extensor moments, leading to high quadriceps activation and increased patellofemoral joint pressure (23). This high mechanical load makes stair climbing a key activity that induces and exacerbates pain in patients with patellofemoral pain syndrome. Among various daily tasks, stair climbing induces the most severe knee pain, followed by stair descending and level walking, highlighting its unique clinical value in assessing symptomatic burden (24). Studies have also shown that abnormal increases in peak knee flexion moment and valgus moment during stair climbing are closely associated with cartilage degeneration and are important mechanical indicators for predicting disease progression (25).

### Targeted exercise therapy

2.12

A personalized exercise protocol is developed based on the patient's clinical status and physical capacity. The protocol comprises periarticular knee muscle strengthening and joint flexibility exercises to enhance lower extremity stability and optimize knee joint load distribution. Strengthening exercises target the vastus medialis obliquus (VMO) and gluteal muscles, specifically including VMO setting and supine bridging. Flexibility exercises are designed to stretch the tensor fasciae latae (TFL), gluteus medius, hamstrings, and gastrocnemius, specifically including supine cross-body stretch and seated hamstring stretch. Each session lasts 30–60 min and is performed twice daily (morning and evening) over a 6-week period, as 6 weeks is the minimum effective duration and compliance dropped after 6 weeks in our pilot data. The specific interventions are described below.

#### Vastus medialis obliquus (VMO) setting (right side as example)

2.12.1

Position: Supine. The left knee is flexed to 90° with the left foot placed flat on the bed. The right leg is extended. The participant contracts the quadriceps, dorsiflexes the ankle, and externally rotates the foot to 30°. The right lower extremity is then elevated until the heel clears the bed surface by 30 cm. The position is held for 10 s, followed by a controlled lowering phase over 10 s (one repetition). A 5 s rest is allowed between repetitions. Ten repetitions constitute one set. Three sets are performed per session, with a 1 min rest interval between sets. Frequency: Once daily.

#### Supine bridge (gluteal strengthening)

2.12.2

Position: Supine with both knees flexed and feet placed flat on the bed, shoulder-width apart. The arms rest along the trunk. The participant inhales, contracts the abdominal and gluteal muscles, and lifts the pelvis by extending the hips until the shoulders, hips, and knees are aligned in a straight line. Core stability is maintained throughout the movement. The end position is held for 10 s, followed by a controlled descent back to the starting position. Ten repetitions constitute one set. Three sets are performed per session, with a 1 min rest interval between sets. Frequency: Once daily.

#### Supine cross-body stretch (right side as example)

2.12.3

Position: Supine. The right hip and knee are each flexed to 90°. The right hand grasps the edge of the bed to stabilize the right shoulder and prevent ipsilateral shoulder elevation. The lumbar spine remains in contact with the bed surface as much as possible. The left hand is placed on the distal right thigh, and a cross-body stretching maneuver is performed until a sensation of tension is perceived in the right gluteal region and lateral right thigh. The stretch is held for 20 s. The procedure is repeated on the contralateral side. Five repetitions are performed per side. Frequency: Once daily.

#### Seated hamstring stretch (right side as example)

2.12.4

Position: Seated with the trunk erect. The right leg is fully extended. The participant shifts the body weight forward and flexes the trunk forward until a stretching sensation is felt along the posterior aspect of the right thigh. The stretch is held for 20 s. The procedure is repeated on the contralateral side. Five repetitions are performed per side. Frequency: Once daily.

### TCM treatment

2.13

#### Oral TCM treatment tailored by syndrome differentiation

2.13.1

For wind-cold-dampness obstruction with blood stasis: Administer Xiao Zeng Qiang Gu Pian (hospital preparation, approval number: Chuan Yao Zhi Bei Zi Z20190330000, 0.25 g/tablet. Main ingredients: Rehmanniae Radix Praeparata, Pyrolae Herba, Cistanches Herba, Spatholobi Caulis, Drynariae Rhizoma, Cibotii Rhizoma, Angelicae Pubescentis Radix, Erythriniae Cortex, Crataegi Fructus (scorch-fried), Massa Medicata Fermentata (scorch-fried), Hordei Fructus Germinatus (scorch-fried). Main efficacy: Tonifies the liver and kidney, dispels wind-dampness.). Dosage: 4 tablets each time, three times daily. Also administer Leng Xi Kou Fu Ye (hospital preparation, approval number: Z20190335000, 10 ml/vial. Main ingredients: Atractylodis Macrocephalae Rhizoma, Morindae Officinalis Radix, Poria, Saposhnikoviae Radix, Cyperi Rhizoma, Achyranthis Bidentatae Radix, Dendrobii Caulis, Dioscoreae Hypoglaucae Rhizoma. Main efficacy: Dispels wind-dampness, strengthens tendons and bones.). Dosage: 10 ml each time, three times daily.

For cases predominantly characterized by wind-damp-heat obstruction with blood stasis: Administer Chuang Shang Xiao Zhong Pian (hospital preparation, approval number: Z20190333001, 7.2 g/box. Main ingredients: Notoginseng Radix et Rhizoma, Panacis Japonici Rhizoma. Main efficacy: Dispels stasis, stops bleeding, reduces swelling, alleviates pain.). Dosage: 3 tablets each time, three times daily. Also administer Xiao Zeng Qiang Gu Pian (as above). Dosage: 4 tablets each time, three times daily, to tonify the liver and kidney, activate blood circulation, and resolve stasis. Oral treatment lasts 6 weeks. Non-steroidal anti-inflammatory drugs (NSAIDs) may be administered orally if necessary.

#### External TCM treatment tailored by syndrome differentiation

2.13.2

For wind-cold-dampness obstruction with blood stasis syndrome: Apply Xin Shang Xiao Zhong San (hospital preparation, approval number: Chuan Yao Zhi Bei Zi Z20190301000, 50 g/bag. Main ingredients: Phellodendri Chinensis Cortex, Rhei Radix et Rhizoma, Corydalis Rhizoma, Paeoniae Radix Rubra, Angelicae Dahuricae Radix, Sargentodoxae Caulis, Notopterygii Rhizoma et Radix, Angelicae Pubescentis Radix, Vladimiriae Radix, Hibisci Mutabilis Folium, Draconis Sanguis, Menthol, Camphora, Borneolum Syntheticum. Main efficacy: Activates blood circulation to resolve stasis, reduces swelling and alleviates pain.) mixed with Angelicae Dahuricae Radix powder (10 g), Asari Radix et Rhizoma powder (10 g), Carthami Flos powder (10 g), and Arisaematis Rhizoma powder (10 g) for external application.

For wind-damp-heat obstruction with blood stasis syndrome: Apply Xin Shang Xiao Zhong San (as above) mixed with Angelicae Dahuricae Radix powder (10 g), Carthami Flos powder (10 g), Paeoniae Radix Rubra powder (10 g), and Arisaematis Rhizoma powder (10 g) for external application.

Specific method for both: Take equal parts (one-quarter each) of Xin Shang Xiao Zhong San and the mixed herbal powder, add an appropriate amount of honey water, and mix into a paste. Apply the paste onto gauze or foam dressing and affix it to the affected knee. Apply externally for 8–12 h each time, once daily. If allergic reactions such as skin itching or redness occur during application, discontinue use immediately. Continuous external treatment lasts 6 weeks.

## Control group

3

This group will receive conventional exercise and the same TCM regimen as the experimental group. The conventional exercise consists of quadriceps exercise (right side as example): supine position with the left knee flexed to 90° and the left foot placed flat on the bed, while the right leg is extended. The participant contracts the quadriceps and dorsiflexes the ankle, then elevates the right leg until the heel clears the bed surface by 30 cm. The position is held for 10 s, followed by a controlled lowering phase over 10 s (one repetition), with a 5 s rest between repetitions. Ten repetitions constitute one set, and three sets are performed per session with a 1 min rest interval between sets. Frequency: once daily for 6 weeks.

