### Group allocation and intervention

2.5

Patients will be assigned to either the experimental group or the control group based on their preference after receiving standardized information about both interventions. Specifically, the experimental group will receive biomechanical monitoring, targeted exercise, and Traditional Chinese Medicine (TCM), whereas the control group will receive conventional exercise and the same TCM regimen as the experimental group.

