#### Statistical analysis

3.2.2

Data will be analyzed using SPSS software (version 26.0, IBM Corp., Armonk, NY, USA). Continuous variables will be presented as mean ± SD, and categorical variables as frequency (n) and percentage (%). The primary outcome is the change in VAS score from baseline to 6 weeks, and an independent samples *t*-test will be used to compare the change scores between the two groups. For outcomes measured at multiple time points (baseline, 6 weeks, 6 months, and 3 years), a linear mixed-effects model will be employed to account for within-subject correlations and to handle missing data under the missing at random assumption, including group, time, and group-by-time interaction as fixed effects and subjects as random effects.

As this is a non-randomized study, baseline characteristics (including age, sex, body mass index, and baseline VAS score) will be compared between groups, and if any significant imbalance is detected, these variables will be included as covariates in the primary analysis to adjust for potential confounding. Secondary outcomes will be analyzed using independent samples *t*-tests for continuous variables and chi-square tests for categorical variables. Missing data will be handled using multiple imputation for sensitivity analysis. A two-tailed *P*-value < 0.05 will be considered statistically significant for all analyses.

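### TCM products differ in part by syndrome, patients choose their arm, and syndrome would be adjusted for only if its imbalance were significant; it should be a prespecified covariate

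*Protocol article*

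**What the plan says.** **TCM in the two arms.** Section 3 (Control group) of the protocol article gives the control group conventional exercise and "the same TCM regimen as the experimental group". Section 2.5 says the same.

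**What the regimen is.** The two parts of section 2.13 are headed "Oral TCM treatment tailored by syndrome differentiation" and "External TCM treatment tailored by syndrome differentiation". Each sets out two alternatives, one for wind-cold-dampness and one for wind-damp-heat, both with blood stasis.

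**Allocation.** Section 2.5 assigns patients "based on their preference after receiving standardized information about both interventions". No stratification or balancing by syndrome is described.

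**Adjustment.** Section 3.2.2 says that "baseline characteristics (including age, sex, body mass index, and baseline VAS score) will be compared between groups", and that "if any significant imbalance is detected, these variables will be included as covariates in the primary analysis". Section 3.1.3 adds a treatment expectation score, used in sensitivity analyses if it differs significantly between groups. The Abstract is broader: it promises adjustment for any variable found to be imbalanced, without saying how imbalance is judged. Syndrome is not named in any of these places.

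**The concern.** The comparison is meant to isolate the exercise programme and its biomechanical monitoring, with TCM held constant. What is held constant is the rule for choosing TCM. The products a patient receives depend on syndrome, and because patients choose their arm, the design does not balance syndrome between arms.

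If one syndrome were commoner in one arm, that arm would differ both in presentation and in part of its medication. The primary outcome is pain at 6 weeks, when the 6-week oral and external courses end. Any effect of syndrome or its products on the VAS change would then be credited to the exercise programme. The planned safeguard is a significance test on baseline variables. With 48 patients per arm, that test can miss an imbalance large enough to matter.

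**Working it through.** **1. What differs between the syndromes (sections 2.13.1 and 2.13.2)**

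| Component | Wind-cold-dampness | Wind-damp-heat | Same? |
|---|---|---|---|
| Oral product 1 | Xiao Zeng Qiang Gu Pian | Xiao Zeng Qiang Gu Pian | Yes, same stated dosage |
| Oral product 2 | Leng Xi Kou Fu Ye | Chuang Shang Xiao Zhong Pian | No |
| External base | Xin Shang Xiao Zhong San | Xin Shang Xiao Zhong San | Yes |
| Added powders (four) | Includes Asari | Includes Paeoniae Radix Rubra | Three of four the same |
| Method and duration | 6 weeks | 6 weeks | Yes |

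The differing oral product for wind-damp-heat ("For cases predominantly characterized by wind-damp-heat obstruction with blood stasis: Administer Chuang Shang Xiao Zhong Pian") is the only oral product whose described action includes pain relief. The external base, used in both syndromes, is also described as relieving pain.

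**2. What the significance screen would miss**

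Inputs: 48 per arm (section 2.6) and a two-tailed 0.05 level (section 3.2.2). The syndrome shares are assumed for illustration. Uncorrected chi-square on a 2 × 2 table:

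- 33/48 against 24/48: χ² = 96 × (33×24 − 24×15)² / (57 × 39 × 48 × 48) = 96 × 432² / 5,121,792 = 3.50, P = 0.061. Not significant, so no adjustment.
- 34/48 against 24/48: χ² = 96 × (34×24 − 24×14)² / (58 × 38 × 48 × 48) = 96 × 480² / 5,078,016 = 4.36, P = 0.037. Significant, so adjustment.

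Against a 24/48 share, the screen therefore lets through a difference of up to 9/48 = 0.1875, about 19 percentage points.

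**3. Size of the resulting bias**

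Bias of the unadjusted difference in mean change = (difference in syndrome share) × (difference in mean VAS change between syndromes, including the effect of their products).

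The second factor is not in the documents. I assume 0.5 to 1.5 VAS points.

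- Lower: 0.1875 × 0.5 = 0.09 points
- Upper: 0.1875 × 1.5 = 0.28 points

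The sample-size section assumes a difference of 1.1 × 2.0 = 2.2 points. Relative to that, the bias is 0.09/2.2 = 4% to 0.28/2.2 = 13%.

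**4. Effect on the primary test**

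With SD 2.0 and 43 analysed per arm (section 2.6), SE = 2.0 × √(2/43) = 0.431. If the exercise programmes truly did not differ, the two-sided rejection rate is 1 − Φ(1.96 − bias/SE) + Φ(−1.96 − bias/SE).

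| Difference in share | Assumed syndrome effect | Bias | Type I error |
|---|---|---|---|
| 18.75 points | 0.5 | 0.09 | 5.5% |
| 18.75 points | 1.5 | 0.28 | 10% |
| 20 points | 1.0 | 0.20 | 7.5% |
| 10 points | 0.5 | 0.05 | 5.2% |
| 40 points | 2.0 | 0.80 | 46% |

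The last row shows how the bias grows. An imbalance of 40 points would be significant at 48 per arm, so the plan's own rule would adjust for it, provided syndrome is among the variables compared.

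**The case against.** Several points on the other side are sound.

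- **The wording on TCM.** A reader might infer that the article contradicts itself by calling a tailored treatment the same regimen. It does not. The control section points back to section 2.13, whose headings announce the tailoring, and the natural reading is one rule applied identically in both arms.
- **The covariate list.** A reader might also infer that syndrome is excluded from adjustment. The list in section 3.2.2 is introduced as non-exhaustive, and the Abstract covers any imbalanced variable. Syndrome is unnamed, not ruled out. The article is condensed, and a full protocol or analysis plan may list more covariates.
- **Link to arm.** Nothing shows that syndrome influences which programme a patient prefers. The choice is between exercise programmes, and TCM follows the same rule in either. The documents support a possibility of confounding, not a prediction of it.
- **Overlap.** The two regimens share most of their content, as the table shows. The description of one product as relieving pain does not establish that patients with that syndrome improve more.
- **General defect.** Choosing covariates by significance test weakens adjustment for every baseline variable, not only this one.

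What remains is narrower. Section 3.2.2 does fix the rule by which a variable enters the primary analysis, and that rule is statistical significance. Bias depends on the size of the imbalance and its relation to outcome, not on its P value. Syndrome merits separate mention because it is the one baseline variable that determines part of the treatment received.

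**Conclusion.** The point holds as an inexpensive improvement, not as the correction of an error. Under the stated rule, a moderate imbalance in syndrome, up to about 19 percentage points against a 24/48 share, would go unadjusted. With an assumed 0.5 to 1.5 point difference in VAS change between syndromes, the bias is about 0.1 to 0.3 points. That is small beside the 2.2 points assumed in the design, and would matter more if the true effect were smaller. The conclusion rests on two quantities that the documents do not give: the syndrome mix in each arm and the effect of syndrome and its products on pain. If either the imbalance or the effect is near zero, so is the bias.

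**What to change.** - **Record** syndrome type at baseline, before the patient states a preference, so that its classification cannot be influenced by the chosen arm.
- **Adjust** for it as a prespecified covariate in the primary 6-week analysis, whatever a baseline test shows. In practice this means a linear model for the VAS change with group and syndrome, in place of the unadjusted t-test. Include syndrome in the mixed models too. Because baseline is one of the four time points there, syndrome should enter with its interaction with time if it is to adjust the change and not only the level.
- **Tabulate** the TCM products received by arm. Section 3.2.1 already has treatment details recorded, so the data should be available.
- **Optionally**, say in sections 2.5 and 3 that both arms follow the same syndrome-based rule. This is clarification only.

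Cost: one degree of freedom in the primary analysis, three more in the mixed models if the time interaction is used (four time points less one), and one table. Syndrome must already be established in order to treat, so no extra assessment is needed. Neither the treatments nor the sample size change. The timing of recording should be settled before enrolment, which section 2.2 schedules from June 2026.

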### Outcome measures

3.1

#### Primary outcome

3.1.1

The primary outcome is pain intensity measured using a 0–10 Visual Analog Scale (VAS), where 0 represents no pain and 10 represents the worst possible pain. The change in VAS score from baseline to each follow-up time point (6 weeks, 6 months, and 3 years) will be used as the primary endpoint.

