**Methods and analysis:**

This single-centre, prospective, interventional cohort study will investigate the effectiveness of a biomechanically monitored targeted exercise protocol combined with Traditional Chinese Medicine (TCM) compared with conventional exercise combined with TCM in patients with patellofemoral pain syndrome (PFPS). We will consecutively recruit 96 eligible patients. Participants will be assigned to either an experimental group or a control group based on their preference after receiving standardized information. The experimental group will receive biomechanical monitoring, targeted exercise, and Traditional Chinese Medicine (TCM), whereas the control group will receive conventional exercise and the same TCM regimen.

Outcomes will be assessed at baseline, 6 weeks, 6 months and 3 years post-intervention. The primary outcome measure will be pain intensity measured using the Visual Analog Scale (VAS). Secondary outcome measures will include: biomechanical parameters; pain (Knee Pain Scale); joint function (Lysholm Knee Scoring Scale); kinetic parameters (mean power and pulling acceleration during stair climbing using the IDEEA system); spatiotemporal gait parameters (walking speed, step frequency, double support time during stair climbing using IDEEA); and quality of life (36-Item Short Form Health Survey).

For statistical analysis, independent samples *t*-tests will be used for between-group comparisons, and linear mixed-effects models will be applied for outcomes measured at multiple time points. To control for expectation bias, patients' treatment expectation scores will be recorded at baseline and adjusted as covariates if significant between-group differences exist. Baseline characteristics will be compared, and any imbalanced variables will be included as covariates in the primary analysis. A two-tailed *P*-value < 0.05 will be considered statistically significant.

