### Sample size

2.6

The sample size for this study was determined through an *a priori* power analysis based on a two-independent-sample means comparison, aimed at detecting differences in the change scores (pre- to post-intervention) of the primary continuous outcome (VAS) between the two groups. Based on previous studies or pilot data, we assumed a mean difference of *δ* = 1.1*σ* between the groups, with an estimated population standard deviation of *σ* = 2.0. The significance level was set at *α* = 0.05 (two-tailed) and the statistical power (1–*β*) at 0.95. Using the corresponding formula (1), a sample size of 43 participants per group was calculated, resulting in a total of 86 participants.$$n_{1}=n_{2}=2{\left(\frac{z_{\alpha /2}+z_{\beta }}{\delta /\sigma }\right)}^{2}$$

To account for potential loss to follow-up or dropouts and to ensure reliable between-group comparisons and data analysis in a real-world setting, the sample size was increased by approximately 10%. Thus, a total of *n* = 96 participants with patellofemoral pain syndrome are planned to be recruited, with *n* = 48 in each group. All eligible patients will be consecutively assessed for eligibility during the study period and assigned to the corresponding intervention group.

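### The primary endpoint is VAS change at three visits in section 3.1.1 but at 6 weeks only in section 3.2.2, with no rule for multiple primary tests

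*Protocol article*

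**What the plan says.** The protocol article defines the primary endpoint in two places.

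- **Section 3.1.1 (Primary outcome):** the VAS change "from baseline to each follow-up time point (6 weeks, 6 months, and 3 years) will be used as the primary endpoint". All three visits are primary.
- **Section 3.2.2 (Statistical analysis):** "The primary outcome is the change in VAS score from baseline to 6 weeks". Only this one visit is primary. Its test is named as well: "an independent samples *t*-test will be used to compare the change scores between the two groups".

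Four other places bear on the question.

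- **Abstract:** names VAS pain intensity as primary and gives no time point for it.
- **Section 2.6 (Sample size):** plans for one between-group difference in pre- to post-intervention VAS change, at two-tailed 0.05 and power 0.95.
- **Section 3.1.2 (Secondary outcomes):** does not list VAS at 6 months or 3 years, so only section 3.1.1 gives those changes a status.
- **Section 3.2.2, later sentences:** "For outcomes measured at multiple time points (baseline, 6 weeks, 6 months, and 3 years), a linear mixed-effects model will be employed" with group, time and their interaction. A two-tailed P-"value < 0.05 will be considered statistically significant for all analyses".

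**The concern.** A trial needs one settled statement of which result decides its claim. Here the outcome section supports three deciding results and the analysis section supports one. The article does not say whether success at one visit is enough, whether all three are needed, or whether the visits are tested in order.

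There are two consequences. First, if three visits are each tested at 0.05 and any one suffices, the overall type I error is above the 5% that section 2.6 plans for. Second, the results come in years apart. A null 6-week result could be followed by a primary claim at 6 months or 3 years. Equally, a failed 3-year result could be set aside because only 6 weeks was primary. Each course would have support in the published text.

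Pre-specification matters more than usual in this study. Patients choose their own group (section 2.5), and the outcome is self-reported, with expectation bias acknowledged (section 3.1.3).

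**Working it through.** **1. Do the passages agree?**

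| Place | Primary time point(s) | Primary tests implied |
|---|---|---|
| Abstract | none named | unclear |
| 2.6 | one pre- to post-intervention change | 1, at undivided 0.05 |
| 3.1.1 | 6 weeks, 6 months, 3 years | 3 |
| 3.2.2 | 6 weeks | 1 (t-test) |

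Sections 3.1.1 and 3.2.2 contradict each other. The Abstract is less specific and does not settle the matter. Section 2.6 fits a single endpoint. It does not name week 6, but treatment lasts 6 weeks (sections 2.12, 2.13 and 3), so that is the natural reading.

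**2. The plan's own sample-size figure.** The inputs from section 2.6 are δ/σ = 1.1, two-tailed α = 0.05 (z = 1.960) and power 0.95 (z = 1.645). The formula printed there gives

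n per group = 2 × ((1.960 + 1.645) / 1.1)² = 21.48, so 22.

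The stated 43 per group is not reproduced. Twice the unrounded value is 42.96, so 43 looks like the total for both groups used as the per-group number. That is a separate matter which errs toward too many patients, and the present point does not depend on it. What matters here is that α enters once and undivided, so the calculation is for one test.

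**3. Type I error with three tests at 0.05 and success on any one.** For independent tests:

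1 − (1 − 0.05)³ = 1 − 0.857375 = 0.1426, or 14.3%.

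The three changes share patients and a baseline value, so positive correlation is expected. The article gives no correlation, so a range is assumed. Each row comes from 2,000,000 simulated sets of three equally correlated standard normal statistics, each compared with ±1.960.

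| Assumed correlation | At least one significant | All three significant |
|---|---|---|
| 0 | 14.3% | 0.01% |
| 0.3 | 13.6% | 0.09% |
| 0.5 | 12.5% | 0.3% |
| 0.7 | 10.9% | 0.9% |
| 0.9 | 8.3% | 2.3% |

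The last column shows that an all-visits rule would not inflate the error when no effect exists at any visit. The article does not state such a rule.

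**4. What keeping three primary visits would cost.** Under Bonferroni each test uses 0.05/3. The required number rises by the factor ((z at 0.05/3 two-tailed + 1.645) / (1.960 + 1.645))² = 1.255, giving 21.48 × 1.255 = 26.96, so 27 per group. With 43 per group, power per test for a 1.1 SD difference would be 99.7%. On the plan's own assumptions, numbers do not stand in the way of a proper multiplicity rule.

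**The case against.** The strongest reply is that section 3.2.2, which specifies the tests, names one endpoint, one test and one threshold before the planned June 2026 start. It sends repeated outcomes to a single mixed model, not to three t-tests. Error inflation needs three separate tests and an any-visit success rule, and the article states no such rule. Requiring all three visits, or using one group-by-time test, would not inflate the error.

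Much of this is right about the numbers. The inflation is conditional, 14.3% is the independence case, and the true figure is probably lower. The link between section 2.6 and week 6 is also an inference.

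The reply does not remove the contradiction. Section 3.1.1 still makes three visits primary, and the article gives no rule that would protect that reading. The mixed model does not help, because no term in it is designated as primary. An analysis plan not shown here could follow one definition only, and would then conflict with the other. Nor is this detail left out of a condensed article: the endpoint is stated twice, differently.

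**Conclusion.** The concern holds and should be corrected before any outcome data are seen. The article gives two incompatible definitions of the primary endpoint and no rule for handling three primary results.

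Under the three-visit reading with success on any one, the overall type I error is about 8% to 14%, against the 5% planned. This rests on the any-visit rule, on assumed equal correlations between 0.9 and 0, and on each test being valid at 5% by itself, which allocation by preference does not guarantee. The contradiction, and the freedom it leaves to choose the endpoint after the results are in, depends on none of these figures.

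**What to change.** In section 3.1.1, name the change in VAS from baseline to 6 weeks as the single primary endpoint, and state the same time point in the Abstract. List the 6-month and 3-year VAS changes as secondary in section 3.1.2, estimated from the mixed model in section 3.2.2. In section 2.6, say that the change used for sizing is the 6-week change.

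Two clarifications belong in the same edit:

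- VAS is itself a repeated outcome, so section 3.2.2 yields a 6-week contrast from both the t-test and the mixed model. State which one is the primary analysis.
- The Abstract and section 2.2 count the visits as post-intervention, while sections 3.1.1 and 3.2.2 count from baseline. State the origin of the 6-week visit.

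The cost is a few sentences, with no new patients, visits or data. The drawback is that durability of effect is no longer a primary claim. If the sponsor wants the later visits to stay primary, the alternative is to write down a rule (a fixed testing order, an all-visits requirement or an adjusted α) and bring sections 2.6 and 3.2.2 into line with it.
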